## Abstract

**Background:**

Excess weight is a major risk factor for chronic diseases. In Australia, over 60% of adults are overweight or obese. The overconsumption of energy-dense nutrient-poor (EDNP) foods and low physical activity (PA) levels are key factors contributing to population obesity. New cost-effective approaches to improve population diet and PA behaviors are needed.

**Objective:**

This 1-year randomized controlled trial (6-month intervention and 6-month follow-up) aims to investigate whether a tailored intervention using mobile technology can improve diet and PA behaviors leading to weight loss in adults (aged 18-65 years) who are overweight or obese and recruited through a social marketing campaign (LiveLighter).

**Methods:**

All eligible participants will provide data on demographics and lifestyle behaviors online at baseline, 6 months, and 12 months. Using two-stage randomization, participants will be allocated into one of three conditions (n=200 per group): tailored feedback delivered via email at seven time points, informed by objective dietary (mobile food record app) and activity (wearable activity monitor) assessment; active control receiving no tailored feedback, but undergoing the same objective assessments as tailored feedback; and online control receiving no tailored feedback or objective assessments. Primary outcome measures at 6 and 12 months are changes in body mass, EDNP food and beverage consumption, and daily moderate-to-vigorous PA (measured via accelerometry). Secondary outcomes include change in fruit and vegetable consumption, daily sedentary behaviors, and cost effectiveness.

**Results:**

Enrolment commenced in August 2017. Primary outcomes at 12 months will be available for analysis from September 2019.

**Conclusions:**

Tailored email feedback provided to individuals may deliver a cost-effective strategy to overcome existing barriers to improving diet and PA. If found to be successful and cost effective, upscaling this intervention for inclusion in larger-scale interventions is highly feasible.

**Trial Registration:**

Australian New Zealand Clinical Trials Registry ACTRN12617000554369; https://www.anzctr.org.au /Trial/Registration/TrialReview.aspx?id=371325&isReview=true

**International Registered Report Identifier (IRRID):**

DERR1-10.2196/12782

## Introduction

### Background

Excess weight is a major risk factor for chronic disease. Recent data indicate that more than 63% of Australian adults are overweight or obese, with higher rates observed in men than in women (68% versus 55%) [1]. The five leading attributable risk factors for burden of disease in Australia are poor diet, high body mass index (BMI), tobacco smoking, high blood pressure, and insufficient physical activity (PA) [2]. Of these factors, diet and PA are recognized as key factors for achieving energy balance in the complex development of overweight and obesity [3]. The 2011-2012 National Nutrition Survey reported that just over half of the adults met the recommendations for two serves of fruit, and only 7% met the recommended intake of five serves of vegetables [4]. Furthermore, 35% of the daily energy intake consumed was from “discretionary foods” (foods considered to be of little nutritional value; often high in saturated fats, added sugar, and salt; and alcohol or “junk” foods) [4]. With respect to PA, in 2011-2012, just 40% of adults met the recommended 30 minutes of daily moderate-to-vigorous PA (MVPA), and only 19% of adults achieved the recommended 10,000 steps per day [5]. Equally concerning, given the link between sedentary behavior, chronic disease, and obesity, 30% of adults reported engaging in more than 5 hours of sedentary leisure activity each day [5].

### Interventions in Overweight and Obese Populations

Key components of effective nutrition and PA behavioral change interventions include self-monitoring, feedback on performance, and goal setting [6-11]. More recently, there has been a move towards digital interventions utilizing mobile technology (eg, mobile apps and short message service [SMS] messaging) to improve population reach, real-time data collection, and feedback delivery [12]. Cost efficiency is a major potential strength of such interventions, and the challenge of ensuring design and implementation is supported by strong theoretical constructs. Although a plethora of healthy eating and weight-loss apps have become available, many lack behavioral strategies in their design [13]. A qualitative review of effective technology-based weight-loss interventions identified five key features related to effectiveness: self-monitoring, positive feedback, social support, controlled program content, and individually tailored feedback [14].

Tailored nutrition and PA interventions have shown promise for behavioral change; nonetheless, the effect size has been small, and most interventions thus far lack objective measures of PA [15-18]. Typically, feedback on behavior change is taken from self-report questionnaires, limiting the scope and relevance of individual diet and PA feedback. With the rapid advances in digital technologies, alternative mediums for delivery of information are now possible, including the use of images and other visual elements [19]. Therefore, interventions incorporating digital features provide a platform to test this concept and address concerns raised about the lack of models to inform the design of digital behavioral interventions [20,21]. For instance, a 6-month tailored intervention using the mobile food record (mFR) app for dietary assessment and tailored feedback improved the diet of young adults [22]. Features such as usability and willingness to continue to use apps may contribute to greater engagement and motivation enhancement by participants [20]. To date, few digital interventions have addressed both diet and PA behaviors together in an overweight population [9,23,24]. A unique aspect of this study is the detailed assessment of dietary intake and PA behaviors to inform tailored feedback.

### Aim

This study will use mobile technologies to undertake detailed assessment of dietary intake and PA behaviors and use these data to formulate personalized tailored feedback for study participants. The overall aim of this 1-year randomized controlled trial (RCT) is to investigate whether a tailored intervention using mobile technology can improve diet and PA behaviors in adults with overweight or obesity, recruited through the LiveLighter social marketing campaign in Perth, Western Australia.

## Methods

### Study Design

This study is a 1-year RCT with a 6-month intervention and 6-month follow-up. Individuals who enroll via the LiveLighter website [25] will be invited to participate and, if eligible, will be randomized to one of three groups: (1) tailored feedback delivered via email at seven time points informed by objective dietary intake (mFR app) and activity (wearable activity monitor); (2) active control receiving no tailored feedback, but undergoing the same objective dietary and activity assessment as tailored feedback; and (3) online control receiving no tailored feedback or objective assessments (Figure 1). All groups will have access to publically available resources via the LiveLighter website. The inclusion of the online control group will distinguish monitoring and tailoring effects from those elicited by exposure to the LiveLighter social marketing campaign and website materials. The project protocol has been approved by the Curtin University Human Research Ethics Committee (approval number HR61/2016) and registered with the Australian New Zealand Clinical Trials Registry (ACTRN12617000554369).

### Recruitment

Participants in the Perth metropolitan area will be recruited using the LiveLighter website [25], LiveLighter social media campaigns, letter-box drops, and radio interviews directing interested individuals to further information and study registration on the LiveLighter website (Western Australia). Potential participants will complete an online consent and screening questionnaire. Staggered recruitment will take place over a 12-month period. To be eligible, participants must be aged 18-65 years, have a BMI ≥ 25 but <40 kg/m^2^, own a mobile telephone (iPhone or Android phone), be able to engage in regular PA, have internet access, and be available to visit a study center in metropolitan Perth. Participants will be excluded on the basis of serious illness or medical conditions including diabetes requiring insulin, renal disease, liver disease; weight loss > 4 kg in the previous 2 months; appetite suppressant use, weight loss, or hormone-replacement medication use; pregnancy or current breastfeeding; current tobacco smoking; daily alcohol consumption > 5 standard drinks; prior or planned weight loss surgery; and regular use of an activity monitor in the previous 12 months.

**Figure 1 figure1:**
[figure not shown]
Study design with randomization to three groups. TF: tailored feedback; AC: active control; OC: online control.

### Randomization

A two-staged block randomization will be used with allocation concealment from the active research team via the use of sealed opaque envelopes. The first randomization will be in blocks of six, with separate sex randomization. Second randomization will be in blocks of four, again with separate sex randomization. Eligible participants will be notified via email and invited to complete an online demographic and lifestyle behaviors questionnaire, as detailed in Table 1, prior to stage 1 randomization to either online control (n=200) or face-to-face (n=400) groups. Stage two randomization will occur at the second study visit to assign face-to-face participants to either tailored feedback or active control. Due to the nature of the intervention, it is not possible to blind participants or researchers to the intervention group postallocation. Sequence generation will be conducted by a biostatistician not involved in the implementation of the trial on site using a randomization table created in Stata (version 15, StataCorp, College Station, TX). The electronic file will be kept in a secure password-protected server by the statistician.

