### Data-Collection Procedures

Following stage 1 randomization, tailored feedback and active control participants will be invited to attend two data-collection sessions with the research team, approximately 1 week apart. At the first baseline visit, participants will receive training in the use of the 4-day mFR [26-28] and hip-worn GT3X+ accelerometer (Actigraph, Pensacola, FL). During the second study visit, participants will return their accelerometer and be interviewed to clarify the content of their mFR images. At this visit, height, body mass, waist, and hip girth will be measured according to the standard protocol [29], and an aerobic fitness test (6-minute walk test) will be conducted [30]. The same assessments will be repeated at 6 and 12 months, along with additional online assessments for all groups (Table 1) at the same time points. All participants will have access to the LiveLighter website resources throughout the intervention and will be encouraged to use the materials that include evidence-based healthy recipes and meal plans [25].

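### Stage 2 uses a single fixed block size of four within sex in an open trial, so up to one third of tailored feedback/active control allocations could be deduced in advance

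*Protocol article*

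**What the plan says.** All statements are in the protocol article.

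- **Block size.** For stage 2, Randomization says: "Second randomization will be in blocks of four, again with separate sex randomization". It mentions no other stage 2 block size and no variation in size.
- **Timing.** "Stage two randomization will occur at the second study visit to assign face-to-face participants to either tailored feedback or active control".
- **Ratio and numbers.** The abstract's Methods plan equal groups: "participants will be allocated into one of three conditions (n=200 per group". Stage 1 feeds stage 2; the online questionnaire is completed "prior to stage 1 randomization to either online control (n=200) or face-to-face (n=400) groups". Stage 2 is therefore 1:1 among at most 400 people, and a block of four holds two of each arm.
- **Blinding.** "it is not possible to blind participants or researchers to the intervention group postallocation".
- **Safeguards.** The article aims at "allocation concealment from the active research team via the use of sealed opaque envelopes", and adds: "Sequence generation will be conducted by a biostatistician not involved in the implementation of the trial on site".
- **What else happens at visit 2.** Data-Collection Procedures has the research team run both baseline visits. At the second, participants hand back the accelerometer and are interviewed about their food-record images. It continues: "At this visit, height, body mass, waist, and hip girth will be measured according to the standard protocol". The 6-minute walk test is also done then.

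**The concern.** Concealment has two parts: the list must be hidden, and the next entry must not be deducible from earlier ones. Envelopes and an off-site statistician deal with the first. A single small block size in an open trial weakens the second, because each block of four must end with two of each arm. Separate lists by sex do not help, since sex is visible and each list can be tallied. Past allocations are also easy to see: only the tailored feedback group is given the wrist-worn monitor and receives feedback written by the research dietitian.

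The contrast at stake is tailored feedback versus active control. By Table 1 it is the only one with measured body mass, food-record intake and accelerometry in both arms. Foreknowledge could act by two routes:

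- **Selection or retention before stage 2.** The team has already met each participant at visit 1. Rebooking, or the effort made to keep a hesitant attendee, could depend on the expected arm.
- **Handling of visit 2 baseline data.** The food-record interview, body mass, girths and walk test take place at the allocation visit. The Statistical Analysis section compares change in the outcomes, so arm-dependent handling of a baseline value would carry into the result. The Power section is based on energy-dense nutrient-poor food intake, which rests on the food record.

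Baseline accelerometry is not open to the second route, because the recording is complete when the device is returned.

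**Working it through.** The article gives no predictability figure, so there is none to reproduce.

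**Inputs.** Block size 4 within sex, at stage 2 (Randomization); ratio 1:1 (abstract, 200 per group); at most 400 people (Randomization). The observer is assumed to know the block size and every earlier allocation in that sex stratum.

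**Certain allocations.** A 2:2 block has C(4,2) = 6 equally likely orderings: AABB, ABAB, ABBA, BAAB, BABA, BBAA. That makes 6 × 4 = 24 positions.

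- Positions 1 and 2 are never certain.
- Position 3 is certain only when the first two match (AABB, BBAA): 2 of 6.
- Position 4 is always certain: 6 of 6.

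Total (2 + 6)/24 = 8/24 = 33.3%. Applied to 400, this is 400/3 ≈ 133.

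**Best guess** (always name the arm with more places left in the block):

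| Position | Probability of a correct guess |
|---|---|
| 1 | 1/2 |
| 2 | 2/3 |
| 3 | (1/3 × 1) + (2/3 × 1/2) = 2/3 |
| 4 | 1 |

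Mean = (1/2 + 2/3 + 2/3 + 1)/4 = (17/6)/4 = 17/24 = 70.8%, against 50% with no information.

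**Alternatives.** The single-size rows are exact enumerations. The mixed rows come from simulating 300 sequences of 200 allocations, with sizes drawn with equal probability. The simulated observer knows the set of sizes but not the order in which they occur, and updates after every allocation. As a check, the same simulation with size 4 alone gave 33.4% certain and 70.8% guessed.

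| Stage 2 blocks | Certain | Best guess correct |
|---|---|---|
| 4 (as planned) | 33.3% | 70.8% |
| 6 | 25.0% | 68.3% |
| 8 | 20.0% | 66.6% |
| 4 or 6 at random | 5.4% | 69.3% |
| 4, 6 or 8 at random | 2.3% | 68.0% |

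Of 400, 2.3% is about 9 allocations, against about 133. Random variation of size therefore removes most of the certainty, which a single larger block does not. It does little to the success of ordinary guessing.

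**Imbalance.** The largest imbalance when a stratum stops part-way through a block is half the block size: 4/2 = 2 as planned, 8/2 = 4 with sizes up to 8.

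**Stage 1, for comparison.** The 200:400 split implies 2:4 in each block of six. The same enumeration gives 13/45 = 28.9% certain.

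**The case against.** The strongest reply is that the article takes concealment seriously and shows no failure of it. The list is made by someone outside on-site implementation and kept in opaque envelopes. Deduction requires a person or shared log that follows each sex stratum in order and also knows the block size, and nothing says such a record is kept. That stands, and it makes one third a ceiling. It does not remove the weakness, because neither safeguard blocks the deduction.

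A reader might infer three stronger things that the article does not support:

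- **That unblinded staff open the envelopes and know a third of allocations beforehand.** The article does not say who opens them. The research team's role is inferred from its running the visit.
- **That publication disclosed the block size during recruitment.** Enrolment began in August 2017 with recruitment planned over 12 months, and 12-month outcomes were due from September 2019. The article is not shown to have been public while envelopes were still in use. Staff knowledge would more likely come from internal documents.
- **That allocation precedes the visit 2 measurements.** The order within the visit is not given, and a condensed article may leave it to the full protocol. Its absence is not an error.

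The routes to bias are also limited. By visit 2, participants have been screened, have completed the online questionnaire and have attended visit 1, so little eligibility discretion remains. The food images are already captured, and anthropometry follows a standard procedure. Finally, 400 is the stage 1 number; anyone lost before visit 2 and not replaced lowers the count below 133. All of this stands and keeps the point modest.

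**Conclusion.** The point holds as a weakness in a stated design choice. With one fixed 2:2 block of four within sex and open allocations, up to 33.3% of stage 2 allocations (at most about 133 of 400) could be deduced with certainty, and up to 70.8% guessed correctly. Both figures assume an observer who knows the block size and has followed every earlier allocation in the stratum. They measure predictability. They do not estimate bias in any outcome, and the article gives no evidence that bias occurred. The plausible routes are selection or retention before stage 2 and the handling of the visit 2 interview and measurements; baseline accelerometry is affected by neither interview nor measurement at that visit. The change is worth making because it is cheap and removes nearly all certain knowledge.

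**What to change.** For any stage 2 sequence not yet allocated, have the independent biostatistician generate permuted blocks of randomly varying size (for example 4, 6 and 8) within sex, with the sizes withheld from the research team. If all stage 2 allocations have been made, there is no list left to change.

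Secondary clarification: confirm that the stage 2 envelope is opened only after the visit 2 food-record interview, anthropometry and walk test are recorded. This protects against knowledge gained by opening the envelope; only the change of blocks addresses deduction beforehand.

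Changing stage 1 is optional, because its baseline questionnaire is completed online before randomization.

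Cost: a new list from the statistician who already holds the sequence, and one sentence in the visit procedure. No extra participants or staff are needed. The drawback is a largest end-of-stratum imbalance of 4 instead of 2 in each sex.

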### Control Groups

The online control group will complete online self-report questionnaires only, while the active control group will also undertake face-to-face data collection and record dietary intake (mFR app) and PA behaviors (accelerometery) at baseline, 6 months, and 12 months. Neither group will receive tailored messaging or feedback on their dietary intake or PA. As an incentive for retention, active control participants will be advised that they will receive feedback upon study completion, and the online control group will be entered into a 6-monthly prize draw to encourage ongoing participation.

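### Tailored feedback and active control contain only participants who reach the second visit, so comparing either arm with online control is not a fully randomised contrast

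*Protocol article*

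**What the plan says.** All passages are in the protocol article.

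- **Stage 1** (Randomization). Participants complete an online questionnaire "prior to stage 1 randomization to either online control (n=200) or face-to-face (n=400) groups". On block size: "The first randomization will be in blocks of six, with separate sex randomization".
- **Between the stages** (Data-Collection Procedures). "Following stage 1 randomization, tailored feedback and active control participants will be invited to attend two data-collection sessions with the research team". The visits are about a week apart, with the mobile food record and accelerometer introduced at the first and reviewed or returned at the second.
- **Stage 2** (Randomization). "Stage two randomization will occur at the second study visit to assign face-to-face participants to either tailored feedback or active control". On block size: "Second randomization will be in blocks of four, again with separate sex randomization".
- **Online control** (Control Groups). "The online control group will complete online self-report questionnaires only".
- **Numbers.** The Abstract (Methods) says "participants will be allocated into one of three conditions (n=200 per group"). The Power section repeats 200 per group and assumes 20% drop-out, with 600 recruited.
- **Purpose of online control** (Study Design). It is there to separate the effects of monitoring and tailoring from those of exposure to the LiveLighter campaign and website.

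**The concern.** The article describes three randomised groups, but two of them come into being only at the second visit. Data-Collection Procedures already calls people tailored feedback and active control participants before stage 2 has assigned them. Someone allocated to face-to-face who misses that visit has no stage-2 arm, so analysing by allocation cannot put that person back into tailored feedback or active control.

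People who attend a study centre twice are likely to differ in motivation from those who do not. If so, the two face-to-face arms are selected on a characteristic related to outcome, and online control is not selected in the same way. Separating monitoring and tailoring from campaign exposure requires comparing active control, and tailored feedback, with online control. At stake is whether those comparisons can be reported as randomised evidence.

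**Working it through.** **1. The stated numbers.** The ratios implied by the target numbers are 1:2 at stage 1 (two online and four face-to-face in each block of six) and 1:1 at stage 2 (two and two in each block of four).

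- Online control: 600 × 2/6 = 200
- Face-to-face: 600 × 4/6 = 400
- Each face-to-face arm: 400 × 2/4 = 200

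The 200/200/200 split is reproduced, but only if all 400 reach the second visit.

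**2. Which contrasts are randomised.**

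| Contrast | Groups as randomised? | Reason |
|---|---|---|
| Tailored feedback vs active control | Yes | Both assigned at stage 2, after the same gate |
| All 400 face-to-face vs online control | Yes, if non-attenders are followed | Both assigned at stage 1 |
| Tailored feedback vs online control | Not fully | One side passed the attendance gate |
| Active control vs online control | Not fully | Same |

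**3. Which measures are affected.** By Table 1, measured body mass, the mobile food record and the accelerometer are used only in the two face-to-face arms. Contrasts with online control therefore rest on measures collected in all three: self-reported height and body mass, the online eating survey and the activity questionnaire, with EQ-5D for the economic evaluation.

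**4. Arm size after loss between stages.** The article gives no figure for the fraction lost, L, so it is an assumption here. Arm size at stage 2 is 400(1 − L)/2. Stage-1 face-to-face allocations needed for 200 per arm at stage 2 are 400/(1 − L), rounded up.

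| Assumed L | Per arm at stage 2 | Face-to-face allocations needed |
|---|---|---|
| 0% | 200 | 400 |
| 5% | 190 | 422 |
| 10% | 180 | 445 |
| 20% | 160 | 500 |
| 30% | 140 | 572 |

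**5. Illustrative size of the selection.** Let D be the difference in mean change between attenders and non-attenders, in SD units, that would exist without any effect of the arms. The attenders' mean then departs from the mean of the whole stage-1 group by L × D.

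| Assumed L | D = 0.25 | D = 0.5 |
|---|---|---|
| 10% | 0.025 SD | 0.05 SD |
| 20% | 0.05 SD | 0.10 SD |
| 30% | 0.075 SD | 0.15 SD |

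L and D are both assumptions. The figures are before any covariate adjustment and ignore later loss in any arm.

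**6. The drop-out allowance.** The 20% is tied to the 600 recruited: 600 × 0.8 = 480, or 160 per group. At L = 20% with no later loss, each face-to-face arm also ends at 160. If the 20% runs from stage 1, it can absorb the loss between stages. The article does not say where it starts.

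**The case against.** Several points on the other side stand.

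- **The key objective comparison is intact.** Statistical Analysis compares two groups without naming them. If these are tailored feedback and active control, that contrast is validly randomised. Placing stage 2 at the second visit even helps it, since assignment comes at the end of the baseline measurement period.
- **The selection is limited.** Under Recruitment, everyone, online control included, must be available to visit a study centre. Everyone is asked for the questionnaire before stage 1, reminders are planned, and baseline value, age, sex, education and area index are possible covariates. This shrinks the problem without removing it: availability is not attendance, and motivation is only partly captured by those covariates.
- **An article may leave analysis sets and the handling of non-attenders to the full protocol.** That is fair, and their absence is not the point. The timing of stage 2 is stated, and it conflicts with the stated purpose of online control whatever analysis set is used.

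Stronger readings are tempting but not supported:

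- A reader might infer that the food record and accelerometer wear must be completed before stage 2. No such condition is given; the only documented gate is reaching the second visit.
- A reader might infer that online control keeps everyone allocated. That is not stated, and the prize draw to encourage continued participation suggests some loss is expected.
- A reader might infer that the trial is underpowered. This would require loss between stages to come on top of the 20%, which the Power section does not say. It also gives no SD from which power could be recomputed.

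**Conclusion.** The point holds for the contrasts between each face-to-face arm and online control, on the measures shared by all arms. It follows from the stated timing of stage 2 and needs no numerical assumption. Tailored feedback vs active control is not affected.

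The direction is plausibly toward the face-to-face arms but is not established, because loss in online control could also be selective. The size cannot be derived from the article; 0.025 to 0.15 SD is an illustration under assumed L and D.

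On numbers, 200 per face-to-face arm at stage 2 is secured only with no loss between stages; at an assumed 10% loss it is 180. Whether this costs power depends on what the 20% drop-out covers, so no shortfall in power is shown.

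**What to change.** 1. Send the 6- and 12-month online questionnaires to all 400 participants allocated to face-to-face at stage 1, whether or not they attend.
2. Analyse face-to-face vs online control by stage-1 allocation on the shared measures.
3. Keep tailored feedback vs active control by stage-2 allocation.
4. Label tailored feedback vs online control, and active control vs online control, as not fully randomised. Adjust them for the data collected before stage 1. Weighting by the inverse probability of attendance is one option, as a sensitivity analysis.
5. State whether 200 per face-to-face arm counts participants allocated at stage 1 or reaching stage 2, and whether the 20% drop-out includes loss between the stages.

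The cost is small. The study database already sends automated survey links and reminders, online assessments at 6 and 12 months are already planned, and the rest is analysis wording. Some non-attenders will not reply, so the stage-1 contrast will itself have missing data. That contrast is also diluted by non-attenders and cannot separate tailoring from monitoring, so the labelled, adjusted contrasts are still needed beside it.
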